### Data management

Source documents will save in a secured and logged Sharepoint and keep by each center in case of medical reports. Documents specific to the trial will be archived by the investigator and the sponsor for 15 years following the end of the study in accordance with national guidelines. Results from the protocol-specific procedures will be collected in paper format and then entered into the eCRF. The assessors enter all other data directly into the eCRF during the visits. Secured login and password will be attributed by a data manager. Data quality in the eCRF will be promoted using range checks for data values. Each missing data item must be coded. Data will later be transferred to a statistical program for analyses. The data will be anonymized 5 years after the termination of the study.

### Non-adherence and dropout data

Participation in the trial is voluntary, and patients will have the right to withdraw consent at any time, for any reason, without any consequence for further medical treatment. All data in this study will be analyzed according to the principle of intention-to-treat (ITT) to reduce the deviation. The reasons and circumstances for study discontinuation will be documented in the CRF. The patients’ participation in this study can also be ended by the investigator if the patient is uncooperative and/or does not attend the study visits. In this case, patient data collected up until the point of removal will be included in the analysis; if too many data are missing (e.g., missing baseline, study visits, and other measurements included in the primary outcome), the patient will be replaced by a new patient. Patients who convert to open surgery will be treated according to the standard of care, based on the findings during surgery. These patients will be excluded from the study, and patient data until this moment will be included in the analysis.

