### Drop-out criteria

Drop-out criteria for patients are as follows: (1) patients withdrew the informed consent form voluntarily; (2) lost to follow-up, no efficacy and safety data were collected; and (3) the investigator ordered to withdraw, such as the patient returned to the ward with an unexpected tracheal tube.

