### Randomization and masking

To ensure the comparability of groups, a stratified block randomization method with stratified factors for age and different surgical methods was adopted. An independent statistician generated the stratified permuted block randomization sequence by using SAS software (version 9.4, SAS Institute, USA). Centralized randomization was conducted by using the Interactive Voice Response service provided by Shang Hai Ashermed healthcare communications co., Ltd. Subjects meeting the criteria will be randomly assigned to the trial group or routine clinical practice group (control group) in a 2:1 ratio. The trial group will be administrated with S(+)-ketamine hydrochloride injection and the control group will receive conventional therapy without S(+)-ketamine hydrochloride injection. The most common usage in conventional therapy is propofol combined with an opioid.

The patients will be randomly allocated via an interactive response technology (IRT) system which is independent of the trial team. For each patient, nobody has any access to known the intervention that will be received during the screening stage. Block randomization will be done at the individual level with a randomization list generated by the IRT provider and will be stratified by age and different surgical types. The trial manager will inform the participant after notification of intervention allocation.

Since this is an open-label pragmatic trial, the investigators, the subjects and the sponsors who give intervention cannot be masked from intervention allocation. Notably, the investigator and pain score assessor is not the same one in this trial. The pain score assessor will not be informed of the grouping situation.

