### Statistical analysis

All statistical analyses will be performed using SAS 9.4 (SAS Institute Inc., USA). All data in this study will be analyzed according to the principle of ITT to reduce the deviation. The categorical data is expressed as numbers (%) and frequency and will be compared with Pearson chi-square or Fisher’s exact test. Continuous data will be expressed as mean ± standard deviations (SD) or median, minimum, maximum, interquartile range (IQR) and will be compared by Student’s *t* test and Wilcoxon rank-sum test.

For the primary endpoints, covariance analysis (ANCOVA) will be used to perform the between-group comparisons and the age and surgery types that are used as stratification factors in the randomization will be included as covariables. The FLACC scale score and NRS score will be analyzed separately, and then the standardized mean differences (SMD) will be combined by using the fixed effect meta-analysis model. To deal with the multiplicity problem caused by the two primary endpoints, the significance level will set be two-sided 0.025 by using the Bonferroni method. In subgroup analysis, according to age, type of surgery, intervention methods (such as drug administration method, dosage, type of other analgesics, presence or absence of nerve block, etc.) and possible combinations (combination plan of study drug and other drugs), subgroup analysis of the primary endpoints will be performed. For secondary endpoints, univariate analysis and multivariate analysis (Generalized Linear Mixed Model (GLMM)) will be used to perform the between-group comparisons. For safety analysis, the Pearson *χ*^2^ test or Fisher’s exact test will be used for comparison between groups. Effect sizes will be reported with 95% confidence intervals. All tests will be two-sided and the significance level is set as 0.025.

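### The rules that exclude, withdraw or replace children after randomisation contradict the promised intention-to-treat analysis and leave both primary comparisons open to selection bias

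*Protocol article*

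**What the plan says.** ITT is stated twice. Under Statistical analysis: "All data in this study will be analyzed according to the principle of ITT to reduce the deviation". Under Non-adherence and dropout data: "All data in this study will be analyzed according to the principle of intention-to-treat (ITT) to reduce the deviation". The Discussion repeats it as a strength of the trial.

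Three rules then remove children:

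- **Investigator-ended participation, with replacement.** Under Non-adherence and dropout data, the investigator may end participation "if the patient is uncooperative and/or does not attend the study visits". Data up to removal are kept. If too many are missing, with the examples "missing baseline, study visits, and other measurements included in the primary outcome", then "the patient will be replaced by a new patient". No threshold is given.
- **Conversion to open surgery.** The same paragraph says: "These patients will be excluded from the study, and patient data until this moment will be included in the analysis".
- **Withdrawal by order.** The Drop-out criteria include: "the investigator ordered to withdraw, such as the patient returned to the ward with an unexpected tracheal tube".

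Tables 2 and 3 place randomisation at the preoperative part of V1. Clinical assessment defines both primary endpoints, the pain-score area and total opioid consumption, over the 48 h after surgery. Under Randomization and masking, "the investigators, the subjects and the sponsors who give intervention cannot be masked from intervention allocation"; only the pain assessor is kept unaware of the group.

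**The concern.** ITT means that every randomised child is analysed in the assigned arm, whatever happens next. Conversion, an unexpected tube, lack of cooperation and missed postoperative visits all come after randomisation. A rule that ends follow-up at such an event makes membership of the analysed group depend on the course after allocation.

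Assigned treatment could influence that membership. The protocol lists agitation, delirium and increased secretions among the common adverse events. It counts emergence delirium, laryngeal spasm, respiratory depression and over-sedation among its outcomes. Cooperation and airway course may therefore be partly results of treatment. The person who ends participation knows the allocation, and the replacement trigger is left to judgement.

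At stake is whether the two primary comparisons are still comparisons of the randomised groups. Recruiting a new child restores the number but not the comparability. An analysis plan cannot recover outcomes that the protocol has stopped collecting.

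**Working it through.** **1. Timing of each event against the endpoints.**

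- *Conversion to open surgery.* It occurs during the operation, after randomisation and before the 48 h window opens. Data up to that moment contain no postoperative pain score and no postoperative opioid use. The child contributes nothing to either primary endpoint.
- *Unexpected tracheal tube.* The trigger is return to the ward, which is after surgery. For children aged 7 or under, FLACC is scheduled at 10, 20 and 30 min, so some scores may exist. If follow-up stops there, the 48 h pain area and the opioid total are incomplete.
- *Lack of cooperation or missed visits.* Replacement applies when important data are missing, and primary-outcome measurements are among the examples.

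**2. The plan's own sample size.** Inputs from Power and sample size determination: d = 0.25, 80% power, two-sided 0.025, 2:1 allocation.

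Control n = (1 + 1/2) × (2.2414 + 0.8416)² / 0.25² = 1.5 × 9.505 / 0.0625 = 228.1, rounded up to 229. Total = 3 × 229 = 687. This reproduces the stated figure, which is not in dispute.

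**3. Precision at 3000 children (2000:1000).** SE = √(1/2000 + 1/1000) = 0.0387 SD.

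**4. Illustration of selection bias.** If a fraction f of an arm is removed, and removed children differ from retained ones by m SD, the arm mean shifts by f × m. With the same m in both arms, bias = (difference in f) × m. The documents give neither f nor m, so every row below is an assumption.

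| Removed, one arm vs the other | m (SD) | Bias (SD) | Bias / SE | Bias / 0.25 |
|---|---|---|---|---|
| equal | any, same in both arms | 0 | 0 | 0% |
| 5% vs 3% | 1.0 | 0.02 × 1.0 = 0.020 | 0.52 | 8% |
| 5% vs 2% | 1.5 | 0.03 × 1.5 = 0.045 | 1.16 | 18% |

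With no true effect, the type I error per endpoint is about 1 − Φ(2.2414 − bias/SE) + Φ(−2.2414 − bias/SE). It rises from 0.025 to about 0.045 in the second row and about 0.14 in the third.

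**5. Is replacement needed for power?** Power is about Φ(0.25/SE − 2.2414).

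- *Overall, 20% lost and not replaced (1600:800).* SE = √(1/1600 + 1/800) = 0.0433. 0.25/0.0433 − 2.2414 = 3.53, so power is above 99%.
- *Per surgery type, assuming four equal types of 750 (500:250).* SE = √(1/500 + 1/250) = 0.0775, and power is 83.8% with no loss. It is 81.7% at 5% loss, 79.4% at 10% and 74.1% at 20%.

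**The case against.** **The loss is neither total nor hidden.** The text keeps data up to removal, never says that a replaced child's data are deleted, and has reasons for discontinuation recorded in the CRF. This stands, and a claim that replacement conceals the loss would be wrong. It does not restore ITT, because the data kept lack all or part of the primary outcome.

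**The replacement rule is narrow.** It follows directly on investigator-ended participation. A reader might infer that converted children and tube cases are replaced too; the text does not say so. For them the problem is exclusion or withdrawal.

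**Tube cases may have early scores.** A reader might infer that these children, like converted ones, have no postoperative score at all. The schedule for ages 7 and under does not support that.

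**Bias is not shown.** Nothing in the documents links conversion to the anaesthetic arm, and children expected to return with a tube are excluded before entry. The rates in the table are invented for scale, and equal removal of similar children gives no bias. This stands. A reader might infer that the results are biased or the randomised comparison already lost; the documents support only exposure to bias. The masked pain assessor limits measurement bias, but not selection by an unmasked investigator.

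**Some loss is unavoidable.** Withdrawal of consent and true loss to follow-up are not faulted. The handling of missing values can be left to the analysis plan.

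**It may be late to change.** By the estimated dates under Trial status, recruitment was probably well advanced at publication. New wording cannot recover 48 h data from children already removed, but it can stop further loss and settle who is analysed.

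**Conclusion.** The point holds as an internal contradiction with consequences for both primary endpoints. Followed as written, the conversion exclusion, the investigator's power to end participation with replacement, and withdrawal by order are incompatible with analysing all randomised children as allocated. That conclusion needs no assumed rate; it rests on the preoperative randomisation and the 48 h endpoint window.

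The size and direction of bias are unknown. The 0.020 to 0.045 SD illustration depends wholly on assumed removal rates and outcome differences. It shows only that at 3000 children a modest imbalance can be of the order of one standard error. It remains well below the planning effect of 0.25 SD.

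**What to change.** - Delete the replacement rule and the exclusion of children who convert to open surgery.
- Reconcile Drop-out criteria, Non-adherence and dropout data and Statistical analysis, so that every randomised child is analysed in the assigned arm.
- Separate the end of study treatment from the end of data collection. Continue FLACC or NRS scores and opioid use to 48 h after conversion, an unexpected tube, lack of cooperation or stopping of study drug, unless consent to data collection is withdrawn. This concerns follow-up and analysis, not clinical care.
- An analysis without these children may be kept as a sensitivity analysis. The missing-data method can stay in the analysis plan.

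**Cost.** The change is one of wording plus follow-up at visits already scheduled; children with an expected stay under 48 h are not enrolled, so most should still be in hospital. Without replacement there will be slightly fewer complete cases. Overall power for 0.25 SD is hardly affected. Within a single surgery type it would fall just under 80% at 10% loss, on the assumption of four equal types.

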### Confidentiality

All data about potential and enrolled participants will be collected in a secure and logged database, in a secure and logged Sharepoint, or behind a double lock for data in paper format. Only anonymized data will be shared.

### Plans to give access to the full protocol, participant-level data, and statistical code

The data sharing process will comply with the principles of good practice, and the data sharing will be conducted in accordance with the regulatory requirements.

### Auditing

Investigators will cooperate with Contract Research Organization, and CRA will be responsible for monitoring and ensuring that the project implementation conforms to GCP.

### Statistical analysis

All statistical analyses will be performed using SAS 9.4 (SAS Institute Inc., USA). All data in this study will be analyzed according to the principle of ITT to reduce the deviation. The categorical data is expressed as numbers (%) and frequency and will be compared with Pearson chi-square or Fisher’s exact test. Continuous data will be expressed as mean ± standard deviations (SD) or median, minimum, maximum, interquartile range (IQR) and will be compared by Student’s *t* test and Wilcoxon rank-sum test.

For the primary endpoints, covariance analysis (ANCOVA) will be used to perform the between-group comparisons and the age and surgery types that are used as stratification factors in the randomization will be included as covariables. The FLACC scale score and NRS score will be analyzed separately, and then the standardized mean differences (SMD) will be combined by using the fixed effect meta-analysis model. To deal with the multiplicity problem caused by the two primary endpoints, the significance level will set be two-sided 0.025 by using the Bonferroni method. In subgroup analysis, according to age, type of surgery, intervention methods (such as drug administration method, dosage, type of other analgesics, presence or absence of nerve block, etc.) and possible combinations (combination plan of study drug and other drugs), subgroup analysis of the primary endpoints will be performed. For secondary endpoints, univariate analysis and multivariate analysis (Generalized Linear Mixed Model (GLMM)) will be used to perform the between-group comparisons. For safety analysis, the Pearson *χ*^2^ test or Fisher’s exact test will be used for comparison between groups. Effect sizes will be reported with 95% confidence intervals. All tests will be two-sided and the significance level is set as 0.025.

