### Objectives

The primary objective of this study is to evaluate the analgesic effect of perioperative administration with S(+)-ketamine hydrochloride injection based on traditional anesthesia strategies on postoperative acute pain in children undergoing surgery. The secondary objectives of this study are (1) to explore the effect of perioperative administration of S(+)-ketamine hydrochloride injection on postoperative emergency delirium, anxiety and depression mood in children undergoing surgery; (2) to evaluate the safety of perioperative administration of S(+)-ketamine hydrochloride injection in children; and (3) to explore the optimal drug regimen of perioperative S(+)-ketamine hydrochloride injection for children, including the influence of administration route, dosage, timing, compatibility, and type of surgery on the end point of the study.

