### Power and sample size determination

This study hypothesis that S(+)-ketamine hydrochloride could significantly reduce pain scores and/or opioid consumption within 48 h after surgery compared with routine clinical practice. Due to the lack of reference for primary endpoint, the sample size will be evaluated under different effect size assumption. Assuming power is 80%, two-sided significant level 0.025, and the ratio of S(+)-ketamine hydrochloride group to conventional group is 2:1, the sample size under different effect sizes is shown in Table 1. As shown, about 687 patients will be powerful enough to detect an effect size of 0.25. The effect size d is defined as *d* = (μ1–μ2)/σ, and Cohen (1988) gave the interpretation of d=0.25 as 25% of σ and defines *d* = 0.2, 0.5, and 0.8 as small, medium, and large effect size. In our study, the used effect size of 0.25 is a relatively small effect size. By considering 4 types of surgery, we decide to include 3000 patients. Patients will stratify by age and surgical approach, and enrolled in a competitive enrollment way until the total number of research centers reached the expected sample size.

**Table 1 Tab1:** The sample sizes under different effect sizes

Control group (*N*)	S(+)-ketamine hydrochloride group (*N*)	Total subjects (*N*)	Effect sizes
58	116	174	0.500
130	260	390	0.333
229	458	687	0.250
357	714	1071	0.200
514	1028	1542	0.167
699	1398	2097	0.143
913	1826	2739	0.125
1155	2310	3465	0.111
1426	2852	4278	0.100

Sample size under different effect sizes assuming power is 80%, two-sided significant level of 0.025, and the ratio of S(+)-ketamine hydrochloride group to conventional group is 2:1

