### Intervention

In the control group, subjects will receive conventional therapy without S(+)-ketamine. There are no restrictions on drugs, doses, and incompatibility; the researchers can choose appropriate medication regimens based on clinical practice, but other NMDA receptor antagonists will not be allowed to use, such as dextromethorphan and amantadine.

In the trial group, S(+)-ketamine hydrochloride will be administrated for general anesthesia for anesthesia induction, maintenance, or postoperative analgesia. In principle, there are no specific restrictions on the dosage, way of administration, timing, and compatibility of S(+)-ketamine hydrochloride injection, but the recommended dosage is given. The recommended dose range for intravenous injection (1) for intravenous injection is as follows: (a) bolus intravenous injection before skin incision, the dose is 0.1–0.25 mg/kg; (b) bolus intravenous injection (dose 0.1–0.25 mg/kg) before skin incision and continuous intravenous infusion (dose of 0.1–0.25 mg/kg/h) during operation; and (c) continuous intravenous infusion after surgery with a dose of 0.02–0.1 mg/kg/h for 24–48 h and (2) for intramuscular injection as the dose is 2–4 mg/kg.

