### Safety assessments, reporting, and harms

Safety of treatment regimens will be assessed by the changes of vital signs, physical examinations, laboratory data, the incidence of adverse events (AEs), and serious adverse events (SAEs). AEs are defined as any unexpected medical event experienced by subjects after drug treatment. It can be manifested as symptoms, signs, diseases, or abnormal laboratory tests, but it is not necessarily inferred that there is a clear causal relationship with experimental drugs. SAEs are defined as any of the following: death, life-threatening events, requirement of hospitalization and prolonged hospitalization, deformities and birth defects, significant/permanent disabilities or organ damages, and important medical events or intervention measures.

Both AEs and SAEs that occurred during drug therapy will be recorded on the case report form (CRF) accordingly. SAEs that are considered related to the study are monitored and reported without delay. Study-specific reportable adverse events, including death, or resulting in a life-threatening situation or significant disability, or requiring inpatient hospitalization or prolongation of existing hospitalization are also being monitored during the trial.

Common AEs include (1) increase of blood pressure and heart rate, and generally do not need to be treated. If necessary, esmolol can be used to relieve (2) increase of secretions, use a negative pressure catheter to suck out the secretions, or use atropine to prevent; (3) blurred vision and diplopia, they are transient and generally do not need to be dealt with; (4) agitation, delirium, separation anxiety, and other psychiatric adverse reactions, they are transient reactions, which can recover spontaneously in the short term without special treatment. Psychological counseling can be given, and benzodiazepines can be given when necessary; (5) nausea and vomiting, generally mild and tolerable, may be alleviated by the use of antiemetics such as Setron, if necessary.

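### A blanket intention-to-treat rule covers harms while adverse events are defined by exposure; harms should also be tabulated by S(+)-ketamine actually received

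*Protocol article*

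**What the plan says.** Under Statistical analysis the protocol article states: "All data in this study will be analyzed according to the principle of ITT to reduce the deviation". The same rule appears under Non-adherence and dropout data. Neither place makes an exception for harms. For safety, Statistical analysis names only the tests (Pearson chi-square or Fisher): "exact test will be used for comparison between groups".

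Under Safety assessments, reporting, and harms the wording turns on exposure: "AEs are defined as any unexpected medical event experienced by subjects after drug treatment", and "Both AEs and SAEs that occurred during drug therapy will be recorded on the case report form (CRF) accordingly". The second safety-related statement is the objective itself: "to evaluate the safety of perioperative administration of S(+)-ketamine hydrochloride injection in children".

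On planned exposure, the Intervention section says that in the trial group "S(+)-ketamine hydrochloride will be administrated for general anesthesia for anesthesia induction, maintenance, or postoperative analgesia". Randomization and masking says that "the control group will receive conventional therapy without S(+)-ketamine hydrochloride injection". No expected rate of non-receipt or crossover is given anywhere.

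**The concern.** Comparing arms as assigned answers a question about a treatment policy. The safety objective asks about giving the drug. The two coincide only when everyone gets what they were assigned.

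Where they diverge, switching pulls the arms together. For an efficacy claim that is usually cautious. For a harm the drug raises it is not, because the excess looks smaller and is harder to detect. A rule covering all data commits the harms tables to this comparison alone.

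The adverse-event definition adds an ambiguity. A trial-arm child who never received S(+)-ketamine is in the as-randomised denominator but, if the drug meant is the study drug, has no period in which an adverse event could count. A control child would never have one. If the drug meant is any anaesthetic, the definition works in both arms, but the article does not say so.

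**Working it through.** **Texts side by side.** The analysis rule goes by assignment (Statistical analysis; Non-adherence and dropout data). The event definition and recording window go by drug treatment (Safety assessments, reporting, and harms). The drug is not specified for controls. The schedules do not settle it: Table 3 (ages 8 to 17) ticks adverse events from the preoperative column of V1, while Table 2 (age 7 and under) starts at the operation.

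**The plan's own figure.** The design inputs are "Assuming power is 80%, two-sided significant level 0.025" and a 2:1 ratio. For d = 0.25, control n = 1.5 × (2.2414 + 0.8416)² / 0.25² = 228.1, rounded up to 229, so the total is 3 × 229 = 687. This matches Table 1. It concerns the primary endpoints and says nothing about harms. Only the significance level and the planned 3000 children (2000 and 1000) carry over.

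**Dilution.** Let p1 be the risk with S(+)-ketamine and p0 the risk without it, and assume that switching is unrelated to a child's underlying risk.

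- Trial arm as randomised: (1 − a)p1 + a·p0
- Control arm as randomised: (1 − c)p0 + c·p1
- Difference: (1 − a − c)(p1 − p0)

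The documents give none of a, c, p0 or p1, so every value below is an assumption.

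| a | c | Factor | Shrinkage |
|---|---|---|---|
| 0 | 0 | 1.00 | none |
| 2% | 1% | 0.97 | 3% |
| 5% | 2% | 0.93 | 7% |
| 10% | 5% | 0.85 | 15% |

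**Power.** The planned test is a chi-square, so the null variance is pooled: power = Φ[(Δ − 2.2414·s0)/s1]. Here s0 = √{p̄(1 − p̄)(1/1000 + 1/2000)}, p̄ is the overall risk, and s1 is the unpooled standard error.

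- 2% versus 4%, no switching: Δ = 0.0200, s0 = 0.00695, s1 = 0.00623, power 76%.
- Same, 10%/5%: risks 2.1% and 3.8%, Δ = 0.0170, s0 = 0.00685, s1 = 0.00623, power 60%.
- 3% versus 5%, no switching: Δ = 0.0200, s0 = 0.00789, s1 = 0.00727, power 63%.
- Same, 10%/5%: risks 3.1% and 4.8%, Δ = 0.0170, s0 = 0.00780, s1 = 0.00727, power 47%.

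At 2%/1% the losses are small: 76% to 73%, and 63% to 60%. An unpooled approximation gives levels some 6 to 8 points higher with a similar loss, but it does not match the planned test.

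**The case against.** The case for leaving the plan alone is substantial.

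- **Switching is not planned.** The article leaves dosage, route, timing and compatibility of S(+)-ketamine open in the trial group, but not whether it is given. Controls are to receive none. This is a single surgical episode with 48 hours of follow-up, so non-receipt and crossover may be rare. This stands: the dilution is conditional and could be negligible.
- **Comparing harms as randomised is legitimate in a pragmatic trial.** It keeps the protection of randomisation. Grouping by receipt loses it, because a decision to give or withhold the drug may depend on the child's condition, with bias in an unknown direction. This stands too, and it rules out replacing the as-randomised table.
- **The direction is not always towards hiding harm.** The listed postoperative events include nausea, vomiting and respiratory depression. The Introduction counts gastrointestinal effects and respiratory depression among the drawbacks of opioids, whose use S(+)-ketamine is hypothesised to reduce. For events it lowers, dilution conceals a benefit. This stands.
- **A safety set is commonly defined in the analysis plan, which is not shown.** This stands as far as it goes: the absence of a named set is no fault here. It does not excuse the sentence that places all data under intention to treat, since a later exposure-based harms analysis would depart from that published rule.
- **The adverse-event definition sets timing, not an analysis population.** Controls also receive anaesthetic drugs, so it could be applied by assigned arm. This is a fair reading, but the text does not state it.

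**Conclusion.** The point holds in a limited form. The stated rule ties harms to assignment alone, the event definition is tied to exposure, and the article does not say how they fit together or what the definition means for controls.

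The size depends wholly on assumed switching: from nothing, through 3% at 2%/1%, to 15% at 10%/5%. In that last case about 15 percentage points of power are lost for the two illustrated harms. These figures also assume that switchers carry the same underlying risk as other children.

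A reader might infer that the plan will make S(+)-ketamine look safer than it is. The documents do not support that: they neither report nor anticipate non-receipt or crossover, and the effect runs that way only for events the drug raises. Nor do they support making a by-receipt table the main harms analysis. A supplementary table and clearer wording are justified.

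**What to change.** Limit the intention-to-treat sentence to efficacy in both sections where it stands. Alternatively, keep it and add that harms are reported two ways: as randomised, and by S(+)-ketamine actually received (any dose or none) among children who had anaesthesia. Show the number of switchers by arm, and state that neither table replaces the other.

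Word the adverse-event definition and recording window so that they apply identically to both arms, for instance by naming a common starting point, and make the two assessment schedules agree with it.

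The cost is a few sentences and one extra set of tables. Tables 2 and 3 already schedule analgesic dosage and concomitant medication during and after surgery. There are two limits. The by-receipt comparison is not protected by randomisation, which is why the as-randomised table must stay. An any-dose grouping also does not date exposure: a child given the drug only after surgery counts as exposed for intraoperative events too, so those need a footnote or exposure dated to that period.

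### With 2:1 allocation, the default pooled variance of the primary ANCOVA miscalibrates standard errors and intervals if the two arms differ in spread; specifying robust or arm-specific variances is a cheap safeguard.

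*Protocol article*

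**What the plan says.** Under Statistical analysis, the test for the two primary endpoints (48 h pain-score area and 48 h opioid consumption) is named: "For the primary endpoints, covariance analysis (ANCOVA) will be used to perform the between-group comparisons". Age and surgery type are the covariates. For pain, FLACC and NRS are analysed separately and their standardized mean differences are pooled by a fixed-effect model. On multiplicity, "the significance level will set be two-sided 0.025 by using the Bonferroni method", while effect sizes are to be reported with 95% confidence intervals. A general sentence in the same section assigns Student's t and Wilcoxon tests to continuous data.

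Under Randomization and masking, patients go to the S(+)-ketamine arm or the "routine clinical practice group (control group) in a 2:1 ratio". Under Power and sample size determination, the calculation uses a single common SD: "The effect size d is defined as *d* = (μ1–μ2)/σ". No numerical SD is given for either primary endpoint in either arm. The article neither states nor excludes a robust or unequal-variance standard error.

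**The concern.** ANCOVA in its default form, and Student's t by definition, estimate one residual variance for both arms. With 1:1 allocation, a difference in spread cancels in the standard error of the mean difference. With 2:1 it does not, because the larger arm dominates the pooled variance while the smaller arm dominates the true variance of the difference.

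A difference in spread is plausible here. Both primary endpoints are amounts that cannot fall below zero, and the spread of such data often falls with the mean. If S(+)-ketamine lowers pain or opioid use as hypothesised, the larger arm may also be the less variable one. That is the direction in which the pooled standard error is too small. What is at stake is the coverage of the reported intervals and, in some situations, the calibration of the p-value that is compared with 0.025.

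**Working it through.** **Inputs from the protocol article.** Sample size basis: "Assuming power is 80%, two-sided significant level 0.025, and the ratio of S(+)-ketamine hydrochloride group to conventional group is 2:1". Planned total: "By considering 4 types of surgery, we decide to include 3000 patients", hence about 2000 versus 1000. Reported intervals: 95%. Critical values: 1.960 for a 95% interval, 2.2414 for a two-sided 0.025 test.

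**Input that must be assumed.** r = SD in the S(+)-ketamine arm / SD in the control arm (residual SDs, in the ANCOVA). The documents give none, so a range is shown.

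**Step 1. Reproduce the plan's own figure.** The plan states that "about 687 patients will be powerful enough to detect an effect size of 0.25". With a common SD, control n = (2.2414 + 0.8416)² × (1 + 1/2) / 0.25² = 9.505 × 24 = 228.1, rounded up to 229. The total is 3 × 229 = 687, which agrees. The other rows of Table 1 also reproduce, apart from one patient in the control group of the 0.333 row (129 against 130). The sample size arithmetic is sound and rests on equal spread.

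**Step 2. Pooled against true variance at 2:1.** In units of (control variance)/(control n):

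- the pooled model uses [(2r² + 1)/3] × 1.5 = (2r² + 1)/2;
- the true value is r²/2 + 1.

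SE ratio f = √{[(2r² + 1)/2] / (r²/2 + 1)}. The sample size cancels, so f does not approach 1 as N grows. At 1:1 both expressions equal r² + 1, so f = 1 for every r.

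Worked case, r = 0.8: pooled (1.28 + 1)/2 = 1.14; true 0.32 + 1 = 1.32; f = √(1.14/1.32) = 0.929.

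**Step 3. Consequences.** Non-coverage of the 95% interval = 2[1 − Φ(1.960 f)]. Rejection at the 0.025 level with equal means = 2[1 − Φ(2.2414 f)].

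| r | pooled | true | f | 95% interval misses | rejection at 0.025, equal means |
|---|---|---|---|---|---|
| 0.7 | 0.990 | 1.245 | 0.892 | 8.1% | 4.6% |
| 0.8 | 1.140 | 1.320 | 0.929 | 6.9% | 3.7% |
| 0.9 | 1.310 | 1.405 | 0.966 | 5.8% | 3.0% |
| 1.0 | 1.500 | 1.500 | 1.000 | 5.0% | 2.5% |
| 1.1 | 1.710 | 1.605 | 1.032 | 4.3% | 2.1% |
| 1.3 | 2.190 | 1.845 | 1.089 | 3.3% | 1.5% |

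**Step 4. Check by simulation.** An ANCOVA with a four-level surgery factor, 2000 versus 1000 patients, equal means and 6000 runs per setting was tested at 0.025. With normal errors, the pooled variance rejected 6.8%, 4.0%, 2.5% and 1.8% of the time at r = 0.5, 0.8, 1.0 and 1.25 (formula: 6.7%, 3.7%, 2.5%, 1.6%). With skewed errors it rejected 6.8%, 3.2%, 2.7% and 1.9%. HC3 standard errors gave 2.3% to 2.8% throughout. Neither the pain-score area nor the pooled standardized mean difference was simulated.

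**Step 5. What r might be.** As an illustration only, zero-inflated opioid use was simulated with assumed users of 70% (control) and 60% (trial), and a mean among users 15% or 25% lower in the trial arm. These inputs correspond to d of about 0.20 and 0.26, near the design value of 0.25. The resulting SD ratios are 0.82 and 0.72. None of these inputs comes from the documents.

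**The case against.** The strongest objection is that the article names a model and not a variance estimator. Robust or arm-specific variance can be requested within an ANCOVA by one option, and such detail usually sits in a statistical analysis plan, which is not shown and may already contain it. This stands to the extent that naming ANCOVA alone is no demonstrated error. It does not cover Student's t, which is the equal-variance test by definition.

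Four stronger readings are tempting, and the documents do not support them.

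- **That the primary p-values are wrong.** This needs unequal spread, and no SD by arm is given. If the drug changes nothing for any patient, the two distributions coincide and type I error stays at 0.025. Inflation needs equal means with unequal spread. If the spread falls because the mean falls, there is a real effect, and the test decision would hardly change: at d = 0.20, z is about 0.20/√(1/1000 + 1/2000) = 5.2 against 2.24. The damage is then to interval coverage.
- **That Student's t drives the primary result.** It stands in the general sentence on continuous data, beside Wilcoxon; the primary test is ANCOVA.
- **That free dosing makes the trial arm the more variable one.** For that arm, "there are no specific restrictions on the dosage, way of administration, timing, and compatibility of S(+)-ketamine hydrochloride injection", but the Intervention section leaves control-arm drugs and doses unrestricted too, apart from barring other NMDA antagonists. The direction cannot be inferred from this.
- **That the pain ANCOVA p-value is the final pain result.** The last step is the pooled standardized mean difference. If it is built on a pooled SD, it carries the same assumption.

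**Conclusion.** The point holds conditionally. Under 2:1 allocation, the default pooled-variance forms of the named methods give miscalibrated standard errors and intervals at any sample size if the arms differ in spread. The effect is modest for SD ratios between 0.9 and 1.1 (95% intervals miss 5.8% to 4.3% of the time) and material at 0.8 or 0.7. Above 1 the intervals are too wide. Lower spread in the larger arm is plausible for non-negative endpoints if the hypothesised reduction occurs, but nothing in the documents shows it. The conclusion rests on an assumed r, on the default variance being used, and on large-sample formulas. It is a worthwhile improvement to the plan; it does not show that the trial's inference is invalid.

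**What to change.** State that both primary ANCOVAs use heteroscedasticity-robust (HC3) standard errors or arm-specific residual variances (in SAS, PROC MIXED with REPEATED / GROUP=arm). State that these standard errors are carried into the fixed-effect pooling of FLACC and NRS. For other continuous comparisons, replace Student's t with Welch's t. If an analysis plan already says this, a cross-reference is enough.

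The cost is one line of wording and one software option. If the variances turn out equal, the loss of precision with about 2000 versus 1000 patients is negligible; in the equal-variance simulations, HC3 rejected 2.5% (normal errors) and 2.7% (skewed errors) against a nominal 2.5%.
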